## ATTACHMENT 1 – Alternative analyses

In addition to comparing R’s for the different presentations, we will examine the relationship between the expected utility model and what participants decide (Eq 1) with how the information about the risk of heart disease was presented in the following ways:

Fit Eq 1 separately for each group G, and estimate the predicted probability of deciding to take the pill, P(D), for each individual based on this model. The best presentation is the one in which the product moment correlation ?(|A- mean(A)|,|P(D)  D|) is smallest. Since the pseudo-residual |P(D)  D| is a measure of how close each individual decision is to the expected decision for that individual, we would expect this to get smaller with increasing distance of A from its mean, m(A), and to do this faster for the better presentation.

Fit Eq 1 separately for each group G, and estimate the Mahalanobis distance M for each model. M is a measure of the "effectiveness of discrimination" of models such as Eq 1; the greater the value of M, the better the model does at discriminating between groups. The n's are the number choosing the pill or not choosing the pill, the SSs are sums of squares from the regression model, and M can be related to a t-distribution, making comparison between presentations straightforward: if one M is significantly larger than all the others, then that presentation results in a model that "discriminates" better than the models resulting from other presentations.

We will also examine alternative ways of analysing the relationship between the expected utility model and what participants decide (Eq 1) with how the relative importance of the consequences of starting statins is elicited (VAS’s vs LTRS’s).

**ATTACHMENT 2** – Risk presentation

| **Presentation  number** |  | **A. Normal risk presentation** | **B. Increased risk presentation** | **C. Decreased risk presentation** |
| --- | --- | --- | --- | --- |
| **1** | **RRR** | Among those who take the pills, there will be a 33% reduced risk of heart disease during the next 10 years. | Among those who take the pills, there will be a 33% reduced risk of heart disease during the next 10 years. | Among those who take the pills, there will be a 33% reduced risk of heart disease during the next 10 years. |
| **2** | **ARR** | Among those who take the pills, there will be a 2% absolute reduction in the risk of getting heart disease during the next 10 years. | Among those who take the pills, there will be an 8% absolute reduction in the risk of getting heart disease during the next 10 years. | Among those who take the pills, there will be a 0.34% absolute reduction in the risk of getting heart disease during the next 10 years. |
| **3** | **NNT** | Among 50 people who take the pills for the next 10 years, there will be one additional person who will not get heart disease during that time. | Among 13 people who take the pills for the next 10 years, there will be one additional person who will not get heart disease during that time. | Among 294 people who take the pills for the next 10 years, there will be one additional person who will not get heart disease during that time. |
| **4** | **Event rates** | Among those who take the pills, the risk of getting heart disease during the next 10 years will be reduced from 6% to 4%. | Among those who take the pills, the risk of getting heart disease during the next 10 years will be reduced from 24% to 16%. | Among those who take the pills, the risk of getting heart disease during the next 10 years will be reduced from 1% to 0.66%. |
| **5** | **TNT** | Among 50 people that take the pills for the next 10 years, they will swallow a total of 182,500 pills and there will be one additional person who will not get heart disease during that time. | Among 13 people that take the pills for the next 10 years, they will swallow a total of 47,450 pills and there will be one additional person who will not get heart disease during that time. | Among 294 people that take the pills for the next 10 years, they will swallow a total of 1,073,100 pills and there will be one additional person who will not get heart disease during that time. |
| **6** | **Whole numbers** | Among 100 people that do not take the pills, 94 will not get heart disease and 6 will get heart disease during the next 10 years. It is not possible to say whether you would be one of the 94 or one of the 6. Among 100 people that do take the pills, 96 will not get heart disease and 4 will get heart disease during the next 10 years. Again, it is not possible to say whether you would be one of the 96 or one of the 4. | Among 100 people that do not take the pills, 76 will not get heart disease and 24 will get heart disease during the next 10 years. It is not possible to say whether you would be one of the 76 or one of the 24. Among 100 people that do take the pills, 84 will not get heart disease and 16 will get heart disease during the next 10 years. Again, it is not possible to say whether you would be one of the 84 or one of the 16. | Among 1000 people that do not take the pills, 990 will not get heart disease and 10 will get heart disease during the next 10 years. It is not possible to say whether you would be one of the 990 or one of the 10. Among 1000 people that do take the pills, 993 will not get heart disease and 7 will get heart disease during the next 10 years. Again, it is not possible to say whether you would be one of the 993 or one of the 7. |

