## METHODS

### Study design

The study is a Web-based randomized trial in which participants will be randomized to one of six ways of presenting information about CVD risk reduction listed above. The relative importance of the consequences of starting statins will be elicited in two ways (VAS’s and LTRS’s) for all of the participants. The order in which this is done will be randomized.

A printout of the Webpages that will be used is attached [Available as a supporting PowerPoint file, Figure S3.1 Facimile HIPPO Webpages for protocol]. Upon logging into the study Website, participants will be given information about the study and asked to give informed consent to participate. They will be presented with a brief scenario in which they are asked to imagine that they have elevated cholesterol and are given the option of taking pills that lower cholesterol (statins). The relative importance of CVD risk reduction, taking pills and costs will be elicited using VAS’s and LTRS’s. They will then be presented with information about the effect of statins on the risk of heart disease, using one of the presentations listed above, the need to take a pill each day and the out-of-pocket costs; and asked whether they would decide to take the pills or not. Baseline risk will then be altered in the direction that shifts the expected utilities towards the opposite decision; i.e. the baseline risk will be increased for respondents who decide not to take the pills and decreased for those who decide to take the pills. Participants will then be asked what they would decide again. After this they will be asked questions about their decision and about themselves and, finally, they will be asked which of the six ways of presenting CVD risk reduction they would prefer.

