### Sample size

Random variation in choices can be expected to be smaller the better risk information is understood. So we will expect a stronger association (larger R2) between the expected utility model (A) and what participants decide (D) the better the information about the risk of heart disease is understood. Turning this around, a significantly stronger association between the model and what participants decide for one presentation (G1) compared with another (G2) suggests that the first presentation was better understood than the second.

The detectability of a difference in magnitude between population R’s is not a simple function of the difference.10 That is, if we were to define j = R1 – R2 and try to use j as the effect size, the detectability of j under fixed conditions of  (level of significance) and sample size n, is not constant, but depends on where along the R scale the difference j occurs. The Fisher Z transformation of R provides a solution to this, and the effect size index q = Z1 – Z2 gives values whose detectability does not depend on whether the Z’s are both small or both large. Cohen considers q = 0.10 as a small effect size, and the following pairs of R’s illustrate this amount of difference: (0.00;0.10), (0.20; 0.29), (0.40; 0.48), (0.60; 0.66), (0.80,0.83), (0.90;0.92), (0.95;0.96). A medium effect size is q = 0.30 and the following pairs of R’s illustrate this amount of difference: (0.00;0.29), (0.20; 0.46), (0.40; 0.62), (0.60; 0.76), (0.80,0.89), (0.90;0.94), (0.95;0.97). A large effect size is when q = 0.50. This is illustrated by the following pairs of R’s: (0.00;0.46), (0.20; 0.61), (0.40; 0.73), (0.60; 0.83), (0.80,0.92), (0.90;0.96), (0.95;0.98).

As we have no prior information about the size of R within any of the information groups, we will conduct a pilot study. The number of subjects to be included in each group in the pilot study is based on power calculations for detecting a medium and a somewhat larger effect size (assuming equal size of the groups):

| q |  (2-sided test) | Power | N |
| --- | --- | --- | --- |
| 0.30 | 0.05 | 0.70 | 140 |
|  |  | 0.75 | 157 |
|  |  | 0.80 | 177 |
|  | 0.10 | 0.70 | 108 |
|  |  | 0.75 | 123 |
|  |  | 0.80 | 140 |
| 0.40 | 0.05 | 0.70 | 80 |
|  |  | 0.75 | 90 |
|  |  | 0.80 | 101 |
|  | 0.10 | 0.70 | 62 |
|  |  | 0.75 | 70 |
|  |  | 0.80 | 80 |

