As can be seen from the table above, the required sample size varies from 80 to 140 per group. However, if we manage to recruit a minimum of 100 subjects into each group, we are likely to obtain estimates for the difference in R’s in addition to estimates of the R for each group.

The total sample size that is needed will be calculated based on the results of the pilot study. Because we are not certain how best to analyse the data, we will also explore alternative ways of analysing the results (see Attachment 2) and, if needed, adjust the sample size calculations to take account of this.

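### The first alternative analysis in Attachment 1 names the presentation with the smallest sample correlation as best, with no measure of uncertainty and no way to report that there is no difference

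*Protocol*

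**What the plan says.** The trial compares six presentations: "participants will be randomized to one of six ways of presenting information about CVD risk reduction". The Analysis section makes the main comparison one of R2 from Eq 1, fitted separately in each group. The Sample size section words the inference for it as "a significantly stronger association between the model and what participants decide for one presentation (G1) compared with another (G2").

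Attachment 1 then sets out further methods, "In addition to comparing R’s for the different presentations". In the first, Eq 1 is fitted in each group, each participant's probability of choosing the pill is predicted, and the distance of A from its mean is correlated with the absolute difference between predicted and actual decision. The rule follows: "The best presentation is the one in which the product moment correlation" is smallest. The reason given is directional only: "we would expect this to get smaller with increasing distance of A from its mean", and faster for a better presentation.

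The second method, based on the Mahalanobis distance, does carry a condition: "if one M is significantly larger than all the others", that presentation discriminates better.

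The Sample size section gives the status of these methods: "Because we are not certain how best to analyse the data, we will also explore alternative ways of analysing the results".

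**The concern.** The rule takes six sample correlations and returns the arm with the lowest. Because P(D) comes from a model fitted to the data of each arm, these are estimates with sampling error, yet the rule treats their order as the answer. It has no outcome for presentations that cannot be told apart. It is the only one of the three ways of comparing presentations that carries no reference to significance.

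What is at stake is limited but real. One aim of the pilot is to settle the method of analysis, and the Sample size section allows the alternatives to change the sample size calculation. A criterion that always yields a clear-looking ranking may appear more decisive than the others when it is only reporting noise.

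**Working it through.** **The plan's own figure.** The protocol computes only one set of figures, the N per group for a difference q between two Fisher-transformed correlations. The formula is n = 2 × ((z for alpha + z for power)/q)² + 3. For q = 0.30, two-sided alpha 0.05 and power 0.80: 2 × ((1.960 + 0.842)/0.30)² + 3 = 177.4, against 177 in the table. At power 0.70 it gives 140.2, against 140. All 12 cells reproduce to the nearest whole number. The table is sound, but it concerns the comparison of R's. The document gives no error rate or precision for the Attachment 1 correlation.

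**Inputs from the protocol.** Six arms; at least 100 per arm in the pilot; 177 as the largest tabulated N; Eq 1 fitted per arm; the smallest correlation wins.

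**Inputs that are assumptions.** The protocol gives no distribution for A and no slope for Eq 1. A is taken as standard normal, with indifference at its mean and slopes of 0.5, 1 and 1.5 per SD of A. There were 3,000 simulated six-arm trials per setting.

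**Step 1: can the rule return no difference?** No. Six continuous statistics always have a minimum, and ties have practically zero probability. This follows from logic and from no assumption. In a second simulation with Beta-distributed scale scores, three assumed coefficient pairs and 100, 140 or 177 per arm, six identical arms gave exactly one winner in 2,000 of 2,000 trials in each of the nine settings. Each arm won in roughly one trial in six (15% to 19%).

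**Step 2: how large is the chance spread?** Six identical arms of 100:

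| Slope per SD of A | SD of the correlation | Mean gap, smallest to largest |
| --- | --- | --- |
| 0.5 | 0.15 | 0.37 |
| 1 | 0.11 | 0.27 |
| 1.5 | 0.08 | 0.20 |

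The gap is about 2.5 SDs throughout (0.37/0.15, 0.27/0.11, 0.20/0.08). The Beta-based simulation gave gaps of 0.25 to 0.36 over 100 to 177 per arm, so the spread does not hinge on normality.

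**Step 3: how often is the wrong arm named when one is truly better?** One arm has a 1.5-fold slope:

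| Slope in the other five arms | Wrong arm, 100 per arm | Wrong arm, 177 per arm |
| --- | --- | --- |
| 0.5 | 64% | 55% |
| 1 | 56% | 44% |
| 1.5 | 67% | 57% |

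At 100 per arm the true effect moves the correlation by only about 0.05 to 0.10. The SD of a difference between two arms is √2 × 0.15 = 0.21 at the lowest slope and √2 × 0.08 = 0.11 at the highest, so noise exceeds signal.

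**Step 4: would an ordinary correlation test do?** No. In the Beta-based simulation the SD at 100 per arm was 0.13 to 0.14, against about 0.10 from the usual formula. A Fisher-Z test of equality at 0.05 rejected in 27% to 47% of trials with equal arms. A resampling method that refits Eq 1 is needed.

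**The case against.** The strongest reply is that the sentence defines a direction and is not a decision rule: it says which way the index points, as a larger R2 does in the Sample size section, and leaves inference to an analysis plan that is not shown. That is a possible reading, and nothing in the protocol rules inference out. But the sentence is worded as a complete selection rule, and the very next method states its significance condition. This is a rule fixed badly, not a detail left for later.

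Three further points stand and limit the weight of the concern.

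- The analysis is exploratory and supplementary. A reader might infer that the trial's main conclusion carries a 100% false-positive rate. The documents do not support this: the main comparison is of R2, its inference is worded in terms of significance, and no section lets this criterion alone decide the result.
- Always naming a winner is true of any ranking. Setting that certainty against 0.05 would import an error rate that the protocol never attaches to this analysis; its table uses both 0.05 and 0.10, and for the comparison of R's. Judged as a selection procedure, the rule does better than chance: it picks the right arm in 36%, 44% and 33% of trials at 100 per arm, against 1/6 = 17%.
- 100 per arm is the pilot minimum, and the full size is to be set from the pilot. At an assumed 400 per arm the wrong-arm rates fall to about 36%, 23% and 38%.

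**Conclusion.** The concern holds in a limited form. The first alternative analysis states a selection rule that takes no account of sampling error and cannot report that the presentations are alike, in contrast to the protocol's other two comparisons. That much rests on the text alone. The chance gaps of 0.20 to 0.37 at the pilot minimum, and the wrong-arm rates of 56% to 67% there and 44% to 57% at 177 per arm, rest on the assumed slopes, a normal A and a 1.5-fold difference in one arm.

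The consequence is a possibly misleading ranking in the pilot's exploration of methods. It is not a fault in the main R2 comparison. This is a minor point, worth considering because the remedy is cheap.

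**What to change.** Replace the selection sentence in Attachment 1 with wording such as:

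> A smaller correlation indicates a better presentation on this criterion. The six values and their pairwise differences are reported with 95% bootstrap confidence intervals (participants resampled within arm, Eq 1 refitted each time) as an exploratory ranking. A presentation is called best only if its intervals against all the other arms exclude zero in its favour.

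The cost is this wording and a few lines of code. The downside should be stated openly. In simulation (300 trials per setting, 300 bootstrap samples, percentile intervals, the same slopes), the truly best arm at a 1.5-fold slope was named in at most 1% of trials at both 100 and 177 per arm. With equal arms a winner was named in at most 0.7%. At pilot size the analysis will therefore almost never name a winner unless differences are very large. Its useful product is the six values and their differences with intervals, which show how little this criterion can separate the presentations at that size.

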## OBJECTIVES

The primary objective of this study is to determine which of the following ways of presenting information about the reduction in risk of cardiovascular disease (CVD) results in decisions that are most consistent with what individuals considering starting statins for the primary prevention of CVD would be expected to decide based on their expected utilities:

1. RRR - Among those who take the pills there will be a 33% reduced risk of heart disease during the next 10 years.
2. ARR - Among those who take the pills, there will be a 2% absolute reduction in the risk of getting heart disease during the next ten years.
3. NNT – Among 50 people that take the pills for the next ten years there will be one additional person who will not get heart disease during that time.
4. Event rates - Among those who take the pills the risk of getting heart disease during the next ten years will be reduced from 6% to 4%.
5. TNT (tablets needed to be taken)10 – Among 50 people that take the pills for the next ten years, they will swallow a total of 182,500 pills and there will be one additional person who will not get heart disease during that time.
6. Whole numbers11 - Among 100 people who do not take the pills, 94 will not get heart disease and six will get heart disease during the next 10 years. It is not possible to say whether you would be one of the 94 or one of the six. Among 100 people who take the pills, the number who will not get heart disease in the next ten years will increase from 94 to 96 and the number who will get heart disease during the next 10 years, will decrease from 6 to 4.. Again, it is not possible to say whether you would be one of the 96 or one of the four.

Additional questions that this study will address are:

1. What is the effect of these different ways of presenting information about CVD risk reduction on understanding, confidence and satisfaction?
2. Which of the following two ways of eliciting the relative importance of the consequences of starting statins for the primary prevention of CVD gives “expected utilities” that are most congruent with what individuals decide?

- Visual analog scales (VAS’s)
- Likert-type rating scales (LTRS)

1. Are answers to the primary question and the two questions above consistent across patients (the general public) and general practitioners (GP’s)?
2. Are answers to the first three questions consistent across different countries (Norway, USA, Canada and Germany)?

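### Attachment 1's smallest-correlation rule for the best presentation is not monotone in consistency: past a moderate A–D association it ranks the more consistent presentation worse

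*Protocol*

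**What the plan says.** The primary objective (Protocol, Objectives) is to find which presentation "results in decisions that are most consistent with what individuals considering starting statins" would be expected to make, given their expected utilities. The main analysis fits Eq 1, a logistic regression of the decision D on the expected-utility difference A, in each group and compares R² (Analysis). The Sample size section expects a larger R² "between the expected utility model (A) and what participants decide (D) the better the information about the risk of heart disease is understood".

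Attachment 1 adds alternatives. The first begins: "Fit Eq 1 separately for each group G, and estimate the predicted probability of deciding to take the pill". It then sets a decision rule: "The best presentation is the one in which the product moment correlation" between |A − mean(A)| and |P(D) − D| takes its smallest value. The reason given is that the pseudo-residual should shrink as A moves away from its mean, "and to do this faster for the better presentation". No range of validity is stated.

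The Pilot study section makes the choice of analysis an aim of the pilot. The Sample size section says that alternatives will be explored and that the sample size may be adjusted to them. (It points to Attachment 2, but the alternatives stand in Attachment 1.)

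**The concern.** The rule treats a faster fall of the residual with distance as the same thing as a more negative linear correlation. These are different. When decisions follow A closely, |P(D) − D| is near zero for almost everyone and large only in a narrow band around the 50% point. A product moment correlation over the whole group then weakens, although the residual does fall faster. In the limit of perfect consistency every residual is zero and the correlation is undefined, so the ideal presentation could not be ranked.

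At stake is a written criterion that could become the trial's method after the pilot and could favour the less consistent presentation, contrary to the objective.

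**Working it through.** The Protocol gives no figure for this rule, so there is none to reproduce.

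**Inputs.** From the Protocol: the rule and Eq 1 (Attachment 1, Analysis) and a minimum of 100 subjects per group (Sample size). Assumed, because the Protocol has no prior information on R: the distribution of A (standardised), the slope b per SD of A, and the position of the 50% point. R² is taken as McFadden's, 1 − logL(Eq 1)/logL(intercept only).

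**Formulas.** If P(D) = p, the residual is 1 − p with probability p, and p with probability 1 − p. Hence

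- E|P(D) − D| = p(1 − p) + (1 − p)p = 2p(1 − p)
- E|P(D) − D|² = p(1 − p)² + (1 − p)p²

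Integrating these over A gives the population correlation r with |A − mean(A)|.

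**Normal A, 50% point at mean(A).** Here p̄ = 0.5, so the intercept-only mean residual is 2 × 0.5 × 0.5 = 0.50. The last column is 1 − mean residual/0.50, from the rounded means.

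| Slope per SD | r | R² | mean residual | scaled reduction |
| --- | --- | --- | --- | --- |
| 1 | −0.48 | 0.14 | 0.41 | 0.18 |
| 2 | −0.62 | 0.33 | 0.30 | 0.40 |
| 2.8 | −0.63 (minimum) | 0.45 | 0.24 | 0.52 |
| 4 | −0.62 | 0.58 | 0.18 | 0.64 |
| 6 | −0.56 | 0.70 | 0.13 | 0.74 |
| 10 | −0.47 | 0.82 | 0.08 | 0.84 |
| 20 | −0.36 | 0.91 | 0.04 | 0.92 |

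R² and the scaled reduction rise throughout; r turns.

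**Other shapes.**

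- Uniform A: minimum −0.67 near slope 3.6, R² about 0.62.
- Normal A, 50% point 0.5 SD from mean(A): minimum −0.44 at slope 1.8, R² 0.30.
- Normal A, 50% point 1 SD from mean(A): minimum −0.21 at slope 0.9, R² 0.11; r is +0.05 at slope 4 and nearly flat after that.

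**Pairs of groups, n = 100, Eq 1 fitted, 50% point at the mean.** The rule prefers the more consistent group in 87% of pairs for slopes 1 v 2, 48% for 2 v 4, 16% for 3 v 6 and 10% for 4 v 8. R² is right in about 97% to 98% of the same pairs.

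**Six arms of 100, one better arm, 1,500 trials.** Chance is 1/6 = 17%. The rule finds the better arm in about 2% of trials (slope 6 against 2), 36% (3 against 1.5) and 61% (2 against 1). The mean residual finds it in over 99%, 95% and 91%. With equal expected take-up, the scaled reduction gave practically the same percentages when rerun.

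**Why scaling matters.** An arm with 90% take-up and no link to A has mean residual 2 × 0.9 × 0.1 = 0.18. That beats 0.30 for a 50% arm at slope 2. Scaled, the first arm scores 1 − 0.18/0.18 = 0 and the second 1 − 0.30/0.50 = 0.40, which is the right order. A simulation set an arm with 80% take-up and slope 0.25 against one with 50% take-up and slope 1, with n = 100 per arm. The unscaled mean picked the more consistent arm about 6% of the time and the scaled version 99%.

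**The case against.** The rule is one of several alternatives, applied in addition to the R² comparison, and R² is monotone in the cases checked. A reversal would show as disagreement between methods. This stands and limits the stakes. It does not remove them, because the pilot's alternatives may shape the final analysis and sample size.

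The clear reversals need a strong association. In the centred normal case the turn at slope 2.8 is an odds ratio of exp(2.8), about 16 per SD of A; slope 6 is exp(6), about 400. The Background expects only some correlation and concedes that utilities are hard to measure. Below the turn the rule orders centred groups correctly and beats chance (36% and 61% against 17%), so there it is inefficient rather than reversed. This also stands for the centred case. It is weaker when the 50% point lies away from mean(A): at 1 SD the turn comes at R² about 0.11, and nothing in the Protocol places the two together.

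A reader might take the pairs of R in the Sample size section as showing that the trial expects values in the reversed range. They only illustrate the effect size q along the scale.

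Reading smallest as smallest in absolute value does not rescue the rule, since an arm with no A–D link has r near 0 and would then rank best.

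The rule is not worse in every setting. In the unequal take-up simulation it picked the more consistent arm in over 99% of trials, where the unscaled mean residual failed. That argues against the unscaled mean as a replacement; it does not make the rule monotone.

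**Conclusion.** The criterion is wrong as a general rule. For normal A with the 50% point at mean(A), it improves with consistency only up to slope about 2.8 per SD (R² about 0.45) and ranks more consistent presentations worse after that. The turn is later for uniform A (R² about 0.62) and earlier when the 50% point is off the mean (R² about 0.30 at 0.5 SD, about 0.11 at 1 SD). At weaker, centred association it orders arms correctly but with less power than R².

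A reader might infer that the trial will name the wrong presentation, or that its primary comparison is compromised. The Protocol supports neither. It gives no slope or R, so whether the data would fall in the reversed range is unknown, and the main R² comparison does not use this rule. The defect is confined to an alternative analysis and can be corrected before any data are collected.

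**What to change.** Delete from Attachment 1 the sentence that identifies the best presentation by the smallest correlation, together with its rationale. The R² comparison can stand without it.

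If a residual-based alternative is kept, define it for each arm as

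1 − mean|P(D) − D| / [2·p̄·(1 − p̄)],

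where p̄ is the arm's proportion choosing pills, or use the analogous squared-residual R². Larger is better. The denominator is the mean pseudo-residual of the arm's own intercept-only model, so lopsided take-up earns no credit. This matters here because the Background cites reviews in which relative risk reduction makes a decision to treat more likely than the absolute measures do. The unscaled mean |P(D) − D| should not be used.

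The cost is one or two sentences. The same Eq 1 fits are used and no new data are needed. The scaled measure rose with the slope in every case checked. In the simulations above it picked the more consistent arm in about 91% to over 99% of trials, including 99% under unequal take-up.

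### Attachment 2, decreased risk: the whole-numbers text (10 to 7 per 1000) shows an absolute benefit about 12% smaller than the 1% to 0.66% behind the ARR, NNT, TNT and event-rates texts

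*Protocol*

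**What the plan says.** Objectives lists six ways of presenting the same reduction in heart disease risk, and Study design randomizes participants between them. After a first decision at normal risk, the baseline risk is lowered for those who chose the pills and raised for those who declined, and each participant decides again. Attachment 2 gives the wording for all three levels. Its decreased-risk column (C) reads:

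- Row 1, RRR: "there will be a 33% reduced risk of heart disease", the same figure as at the other two levels and with no baseline given.
- Row 2, ARR: "there will be a 0.34% absolute reduction in the risk".
- Row 3, NNT: "Among 294 people who take the pills for the next 10 years", with one additional person spared.
- Row 4, event rates: the risk "will be reduced from 1% to 0.66" per cent.
- Row 5, TNT: 294 people and 1,073,100 pills.
- Row 6, whole numbers, per 1000: without pills "990 will not get heart disease and 10 will get heart disease"; with pills "993 will not get heart disease and 7 will get heart disease".

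The whole-numbers text also appears in Objectives, item 6, at normal risk. There it states the change outright ("the number who will not get heart disease in the next ten years will increase from 94 to 96"). Row 6 column A of Attachment 2 gives two separate counts and leaves the reader to work out the change.

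**The concern.** The randomized contrast is the format, so all six texts at a given risk level should carry the same effect. In column C, row 6 does not carry the effect of rows 2 to 5. The comparison with row 4 shows this most plainly: both rows give the risk with and without pills, so wording alone should separate them, yet one implies 0.70% on treatment and the other 0.66%.

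If second decisions in the whole-numbers arm differ from those in the other arms, part of the difference could come from the smaller displayed benefit and not from the format. The two whole-numbers wordings raise a related but secondary question: in a trial of wording, the protocol should say which of them is tested.

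**Working it through.** **Inputs.** All event rates, counts and NNTs come from Attachment 2. The formulas for expected utility come from the Analysis section. Pills per person over ten years: 10 × 365 = 3650.

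**Formulas.** ARR = PN − PP; RRR = (PN − PP)/PN; NNT = 1/(PN − PP); TNT = NNT × 3650.

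**Reproducing the plan's own figures (rows 2 to 5, column C).**
- ARR: 1% − 0.66% = 0.34%, as stated in row 2.
- NNT: 1/0.0034 = 294.1, shown as 294 in row 3.
- TNT: 294 × 3650 = 1,073,100, as stated in row 5.
- Implied RRR: 0.34/1 = 34%.

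Rows 2 to 5 therefore describe one effect.

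**Row 6, column C.**
- ARR: (10 − 7)/1000 = 0.30%.
- RRR: 3/10 = 30%.
- NNT: 1/0.003 = 333.3.

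**Row 1, column C.** A 33% reduction from 1% gives 0.67%, so ARR 0.33% and NNT 1/0.0033 = 303. This is one point of RRR from rows 2 to 5, and participants in this arm see no baseline.

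| Column C | ARR | RRR | NNT |
| --- | --- | --- | --- |
| Rows 2 to 5 | 0.34% | 34% | 294 |
| Row 1 (at 1% baseline) | 0.33% | 33% | 303 |
| Row 6 | 0.30% | 30% | 333 |

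**Size of the mismatch.** Row 6 against rows 2 to 5: 0.34 − 0.30 = 0.04 percentage points; 0.04/0.34 = 11.8% smaller; NNT 333.3/294 = 1.13, so 13% larger. The source is the rounding of 6.6 per 1000 to 7.

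**Other columns.** In column A, 6% to 4% gives ARR 2%, NNT 50, 50 × 3650 = 182,500 pills and RRR 33.3%; all six rows agree. In column B, 24% to 16% gives ARR 8% and NNT 12.5, shown as 13; 1/13 = 7.7%, and 13 × 3650 = 47,450 pills as stated.

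**Effect on A.** Subtracting the two expected utilities in Analysis gives

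A = (PN − PP)(2·VAS_hrt − 1) − VAS_pill − VAS_cost.

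Replacing 0.0034 by 0.0030 changes A by 0.0004 × (2·VAS_hrt − 1). Since VAS_hrt lies between 0 and 1, the change is at most 0.0004 in absolute value. The pill and cost terms can each range from 0 to 1.

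**The case against.** The strongest reply is that this is one rounded cell in a format that is called whole numbers, and that 6.6 (or 6.7, from a one-third reduction) per 1000 rounds to 7. That is correct as to the cause, and it limits the point.

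Column B also contains rounding. Its NNT of 13 is 8 − 7.7 = 0.3 percentage points away from the stated 8%, a larger absolute gap than the 0.04 points in column C. In relative terms it is about 4% (0.31/8) against 12%. Column B thus shows that rounding was tolerated elsewhere; it does not make the row 6 figure agree with rows 2 to 5.

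A reader might infer more than the documents support:

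- That the arms show several different effects at decreased risk. They do not: rows 2 to 5 agree with one another, and row 1 is off only by rounding.
- That presentation is confounded with size of benefit in the trial as a whole. Column C is shown only for the second decision and only to those who first chose the pills. The normal-risk texts agree in every format.
- That participants in the whole-numbers arm are assigned an A that does not match what they read. Analysis defines PN and PP as symbols and gives no value by arm or risk level, so an arm-specific value is not excluded. Even a common value would shift A by no more than 0.0004.
- That a planned comparison of switching rates is biased. Neither Analysis nor Attachment 1 names switching as an outcome; the planned comparison is of the fit of Eq 1 between groups.

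On the wording, the numbers in Objectives item 6 and row 6 column A are identical, and the Web page facsimile is a separate file that is not at hand. Which text participants will read cannot be checked here. What stands is that the protocol contains two wordings for one intervention.

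**Conclusion.** The point holds as a minor but real inconsistency in the randomized material. At decreased risk, row 6 shows an ARR of 0.30% where rows 2 to 5 show 0.34%, about 12% less. For the second decision of those who first chose the pills, the whole-numbers format is therefore not cleanly separated from effect size. The first decision is untouched, and any effect on R² that runs through A is negligible. What remains is a possible effect of the displayed figure on the decision itself. The documents give no basis for estimating its size, nor the share of participants who will see column C.

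This rests on two assumptions: that the Web pages carry the Attachment 2 text, and that A is computed as written in Analysis. The difference in whole-numbers wording is a secondary matter to reconcile.

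**What to change.** Before launch, make every cell of column C describe the same effect. Two routes would do this:

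1. Restate row 6 per 10,000: 100 with heart disease without pills and 66 with them (9,900 and 9,934 free of disease). This gives ARR 34/10,000 = 0.34% and NNT 294, matching rows 2 to 5. It changes only one cell and keeps the 1% baseline, but leaves row 1 one point off (33% against 34%).
2. Use a pair that suits every format, such as 0.9% to 0.6%: RRR 0.3/0.9 = 33%, ARR 0.3%, NNT 1/0.003 = 333 after rounding, 333 × 3650 = 1,215,450 pills, and 9 to 6 per 1000. This aligns all six rows and keeps the one-third reduction of columns A and B, but rewrites rows 2 to 6.

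Whichever is chosen, use in A the PN and PP that are displayed. Bring Objectives item 6 and row 6 column A to one wording, and use that wording on the Web pages. The cost is a text edit to Attachment 2, Objectives and the Web pages; no extra participants are needed.
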